## Abstract

Randomized controlled trials have demonstrated responses to clinical parameters, but a significant proportion of allergy patients in real-life settings would have been excluded from such studies. Therefore, real-world research is needed, and there is a growing body of information on allergen immunotherapy’s long-term effectiveness and safety. Real-world evidence can be a valuable instrument to better understand the patient’s journey and the effectiveness and safety of therapies. For this purpose, a registry will be used for the first time in Italy to evaluate the impact of allergen immunotherapy on several outcomes, including quality of life and disease-related effects in the pediatric and adult allergic population with a socio-economic assessment and respect to real-world health.

## 1. Background

Allergen immunotherapy (AIT) consists of administering increasing amounts of a specific allergen, to which the patient is allergic, at regular intervals for a long time (usually three to five years) to modulate the response of the patient’s immune system to the same allergen [1,2,3]. Although novel applications and delivery strategies are regularly proposed, AIT is currently used to treat allergic respiratory diseases (allergic rhinitis and allergic asthma), food allergy, and insect venom allergy [3,4]. For the scope of this article, regarding the term AIT, we will refer to allergic rhinitis and allergic asthma treatment only; this therapy is offered to individuals who are affected by immunoglobulin E (IgE)-mediated allergic rhinitis and/or allergic asthma due to inhaled allergens, such as pollens, house dust mites (HDMs), molds, or pet danders.

Unlike conventional pharmacotherapeutic approaches (e.g., antihistamines, leukotriene-receptor antagonists, and inhaled and systemic corticosteroids), which act to reduce/control signs and symptoms, AIT can be considered the only disease-modifying treatment in the aforementioned diseases, as it has been shown to modify the natural evolution of type 2 IgE-mediated diseases and to provide long-lasting effect in terms of responsiveness to selected allergens [5,6,7]. In fact, AIT acts on different aspects of the immune response: it reduces IgE-mediated mast cell degranulation, induces Treg cell activation, and promotes the production of allergen-specific IgG4 antibodies that block the IgE activation mediating the inflammatory cascade [7,8]. Moreover, especially in children and young people, AIT might reduce the risk of developing clinical manifestations of asthma and of using asthma medication in the future, arresting the so-called “allergic march” [9,10].

The two main administration routes are subcutaneous immunotherapy (SCIT) and sublingual immunotherapy (SLIT). Both have been proven effective and safe, and each administration route has pros and cons [11].

Interestingly, AIT has been used for over a century, when in 1911 Leonard Noon was the first to show that repeated injections of crude grass pollen extract into individuals with hay fever reduced allergic sign and symptoms to the exposition of the grass pollen [12], a strategy perhaps conceived in analogy with prophylactic vaccination using killed or modified causal organisms for the prevention of infectious diseases; in fact, the term “pollen vaccination” is sometimes used to inaccurately yet effectively indicate AIT.

Over the years, AIT has collected crescent evidence on the efficacy [1,2], safety [13,14,15,16,17], short-term benefits, and long-term benefits, years after its discontinuation [15,18,19]; these achievements have led to important international recognition, with two milestones: the 1998 position paper by the World Health Organization (WHO) [1] and the 2013 World Allergy Organization (WAO) position paper [2]. Nevertheless, an urgent need for quality real-world data has arisen in the same documents.

Numerous random controlled trials (RCTs) have been conducted during the history of this more-than-century-old therapy, and they have provided the necessary evidence for the registration of several AIT products. Indeed, currently, AIT is cited in the most significant and updated international recommendations on the management of allergic rhinitis [20] and asthma [21,22].

Nonetheless, it is well known that RCTs are inherently difficult to conduct, and the ones that evaluate AIT are even more so due to the long span of therapy, the heterogeneity of patients, and the lack of reliable biomarkers [23].

As advocated by the Respiratory Effectiveness Group [24], the RCTs and real-life data such as registries are two equally essential methods and should be used complementarily in defining the effect of an intervention to evaluate the effectiveness of a given therapeutic intervention [25].

This article describes a protocol for a prospective multicenter registry for adults and children starting AIT. The existence of a specific, rigorous, and well-conducted registry would provide high-quality robust data to evaluate the short and long-term effectiveness of this therapy.

Moreover, there is a crucial and urgent need to create a standardized national dataset to facilitate interoperability, data sharing, and cross-comparison among centers. This mass of information might gain sufficient statistical power to address important clinical and research questions, and a national registry will minimize the variability of data collected by standardizing variables across geographical regions, thus enhancing our understanding of the allergic population by examining the response to AIT based on characteristics like phenotypes, biomarkers, concomitant treatments, and socio-economic status. Finally, long-term patient follow-up will enable a real-life understanding of respiratory allergic disease evolution when treated with AIT.

## 2. Methods

### 2.1. Registry Design and Governance

The Italian Registry of Allergy Immunotherapy (RIAIT) is a multicenter observational study that aims to collect the most extensive data available on Italian patients using AIT for respiratory allergies (rhinoconjunctivitis and/or asthma) in a real-life context, through a network of allergy reference centers with specific interest and expertise in the management of allergic respiratory patients.

Following this objective, the registry’s network aims to build an extensive database of patients treated with AIT, gaining the opportunity to collect Italian data and aiming to monitor the evolution of the disease over time during undergoing AIT.

The registry is promoted by the Italian Society of Allergy, Asthma and Clinical Immunology (SIAAIC) [26] and the Italian Society of Pediatric Allergy and Clinical Immunology (SIAIP) [27].

The Italian Society of Allergy, Asthma and Clinical Immunology (SIAAIC) is the biggest Italian scientific society of allergy and clinical immunology; founded in 1953, it is strongly represented on the Italian national territory with over 1700 active members and various thematic areas of interest such as respiratory diseases, dermatologic diseases, allergology, and clinical immunology. The Italian Society of Pediatric Allergy and Clinical Immunology (SIAIP) was founded in 1997 and aims to increase the spread of allergological and immunological culture, not only in the scientific world, but also in society in general, taking into account the negative burden that allergic diseases often have on the health and quality of life of children and their families.

### 2.2. Study Design

This is a prospective multicenter observational registry of patients suffering from conjunctivitis, rhinitis, and/or allergic asthma eligible for and treated with AIT according to EAACI (European Allergy and Asthma Immunology) Guidelines [21].

#### 2.2.1. Inclusion and Exclusion Criteria

The registry will enroll consecutive patients who must meet all the following inclusion criteria:Age ≥ 1 year.Confirmed diagnosis of allergic rhinitis, conjunctivitis, and/or allergic asthma according to EAACI 2019 guidelines [21]. The confirmation of allergenic sensitization must be documented by skin prick tests and/or serum specific IgE.Having been followed by the recruiting center for at least one month. This is considered necessary to establish that the patients are genuinely affected by allergic respiratory disease and are eligible for AIT; in this period, screening tests are carried out to exclude and/or confirm concomitant diseases (comorbidities). In fact, according to the aforementioned EAACI guidelines [21], a patient can be defined as genuinely eligible for AIT only after a preliminary phase in which the patient is treated with a therapy targeted to the clinical manifestations. This observation period allows a correct evaluation of the real adherence and response to therapy, as well as the identification and appropriate treatment of any comorbidity and the possible elimination of aggravating factors.Having received the prescription of any of the available AIT products in Italy, irrespectively of the selected allergens and the administration route and schedule.

There will be no exclusion criteria to allow a real-life vision of the characteristics of these patients eligible for or treated with AIT.

#### 2.2.2. Data Collection

Patients’ available data, including anamnestic, clinical, radiological, and bio-humoral characteristics, will be collected at enrolment and every 12 months thereafter, for a maximum follow-up period of 10 years, through an electronic case report form (eCRF) developed with the REDCap^®^ (Research Electronic Data Capture) software (v14.1.2).

The eCRF compilation can also occur through a Uniform Resource Locator (URL) generated through the REDCap software.

Variables collected at the baseline and every 12-month follow-ups include the following:○Anthropometric characteristics (age, height, gender, and body mass index BMI).○Clinical characteristics (presence of rhinitis and/or conjunctivitis and/or asthma; allergen sensitizations assessed by means of skin prick tests and/or serum specific IgE; presence of comorbidities; lung function parameters; need for hospitalizations and/or visits to the emergency room in recent years, etc.).○Patients’ reported outcomes (PROs): e.g., Rhinoconjunctivitis Quality of Life Questionnaire (RQLQ) [28], Pediatric Rhinoconjunctivitis Quality of Life Questionnaire (PRQLQ) [29]; level of control of rhinitis and/or asthma in the last month, according to Allergic Rhinitis and its Impact on Asthma (ARIA) guidelines [30] and with standardized questionnaires, such as the Total Nasal-Symptom Score (TNSS) [31], the Asthma Control Test Asthma (ACT) [32], and the Asthma Control Questionnaire (ACQ) [33]; the RhinAsthma Patient Perspective (RAPP) [34]; the Asthma Quality of Life Questionnaire (AQLQ) [35]; and the Pediatric Asthma Quality of Life Questionnaire (PAQLQ) [36].○Dosage and posology pharmacological therapies for allergic rhinoconjunctivitis and/or asthma.○Dosages and posology of drugs used for treating comorbidities (e.g., rhinosinusitis; Gastroesophageal Reflux Disease, GERD; atopic dermatitis, etc.).○Allergen immunotherapy details: type and name of the product, given allergens, route of administration, posology, and dosage.○Report and classification of adverse reactions during treatment with traditional drugs and/or AIT.○When available, indirect biomarkers of type-2 inflammation, e.g., as blood eosinophils, serum IgE, and fractional exhaled nitric oxide (FeNO); and lung function parameters.○Adverse events and any reasons for any interruption or switch of AIT.

Any further tests aimed at better phenotyping allergic rhinitis and/or bronchial asthma will be taken into consideration based on the availability of each recruiting center. No genetic investigations or other investigations are planned at the moment.

#### 2.2.3. Objectives

Our objectives include the following:○Evaluate the short- and long-term real-life effectiveness and safety of AIT overall, in specific patient groups’ phenotypes and with specific AIT products.○Evaluate the pertinence and differences in suggesting AIT to a patient, comparing the physician’s evaluation in various settings with established international guidelines, describing the factors associated with treatment choices and changing over time, and promoting interoperability, data sharing, and cross-comparison among centers.○Describe long-term respiratory allergic disease evolution in patients treated with AIT, especially in the pediatric population.○Describe the natural history of the patient population with respiratory allergies and identify patient groups describing their illness burden, management patterns, and clinical progression.○Promote the creation of accurate, standardized, and efficient processes for diagnosing and treating respiratory allergic diseases, especially with AIT.○Assess biomarker data to predict diagnosis, treatment response, and long-term disease progression.

#### 2.2.4. Pharmacovigilance

The data collected also regards the frequency and grading of immediate and delayed and local and systemic adverse reactions attributable to the administration of AIT, as well as the resulting therapeutic management of the events.

#### 2.2.5. Duration of the Study and Statistics

The aforementioned data will be collected for 10 years for each patient. Additionally, periodic statistical analyses will be conducted by the study’s central data manager. The main target will be describing the enrollment trend in the various centers, evaluating the completeness of the information collected, and quality control. The following register comprehensiveness indicators for each center will include the following: the number of patients recruited, the percentage of patients recruited compared to the expected target, and the percentage of missing data per variable. Moreover, descriptive analyses will be conducted to display the distribution of the main characteristics of patients by each center (e.g., sex, age, comorbidities, allergen sensitization profile, the severity of the disease, outcomes, ongoing therapies, etc.).

Quantitative variables will be expressed as mean and standard deviation (or median and interquartile range if distributed asymmetrically). Qualitative variables will be expressed as absolute frequencies and percentages.

The calculation of statistical power or precision is calculated on the basis of the existing sample size. The normality of the continuous variables will be evaluated with the Kolmogorov–Smirnov test. Differences between groups among qualitative variables will be analyzed with the chi-square test or Fisher’s exact test depending on their distribution. Differences between groups among quantitative variables are analyzed via Student’s t-test or Mann–Whitney, on the basis of their distribution.

A two-tailed *p*-value with values inferior to 0.05 will be considered significant. Multivariate or univariate linear regression analyses will be performed among the variables based on a 95% confidence interval. Advanced statistical models, such as the Generalized Estimating Equation (GEE) or the Generalized Linear Model (GLM), will be used to identify responders and non-responders.

A medical data review will also be carried out once a year. These analyses allow for the identification of any corrective interventions aimed at improving the quantity and quality of the information collected among those provided in the CRF; these suggestions will be communicated to the manager of the individual center. The results of the analyses will be published anonymously (as aggregated data) in annual reports, which will be made available to the Principal Investigators of the centers and investigators involved in the project. The results of the analyses carried out will be the subject of scientific publications.

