#### 2.2.7. Ethics

The latest revision of the Helsinki Declaration, as well as the Oviedo Declaration, are the basis for the ethical conduct of the study. The study protocol is designed and will be conducted to ensure adherence to the principles and procedures of Good Clinical Practice and to comply with Italian laws, as described in the following documents and accepted, with their signature, by the study investigators:ICH Harmonized Tripartite Guidelines for Good Clinical Practice 1996.Directive 91/507/EEC, The Rules Governing Medicinal Products in the European Community.Legislative Decree n.211 of 24 June 2003.Legislative Decree n.200 of 6 November 2007.Ministerial Decree 21 December 2007.

The study protocol has been approved by the Central Ethics Committee (Comitato Etico Indipendente Humanitas, protocol number: 2732/2020, and subsequent amendments) and the enrollment in the other centers will start upon approval of each local Ethics Committee.

Together with the British Society for Allergy & Clinical Immunology (BSACI) Registry for Immunotherapy (BRIT) [39] and the international South-Eastern European Adverse Events Registry (ADER) [40,41], this is one of the first registries of patients who are eligible for and benefit from AIT that has been established and this will be a pilot project to be shared with other countries through the European Academy of Asthma Allergy and Clinical Immunology (EAACI) [42].

Inclusion criteria, observation time, and data collected are summarized in Figure 1.

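### The one stated test for qualitative variables ignores time on treatment; used on cumulative yes/no adverse reactions, it could make the less-exposed product or phenotype look safer

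*Protocol article*

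**What the plan says.** Section 2.2.5 of the protocol article gives a general rule for qualitative variables. They are summarised without a person-time denominator: "Qualitative variables will be expressed as absolute frequencies and percentages". Groups are then compared as follows: "Differences between groups among qualitative variables will be analyzed with the chi-square test or Fisher’s exact test depending on their distribution". Two-sided p-values below 0.05 count as significant. The other methods named are the t-test or Mann–Whitney test, linear regression, and GEE or GLM; the last two are assigned to separating responders from non-responders.

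The first objective in section 2.2.3 includes safety: "Evaluate the short- and long-term real-life effectiveness and safety of AIT overall, in specific patient groups’ phenotypes and with specific AIT products". Section 2.2.4 collects "the frequency and grading of immediate and delayed and local and systemic adverse reactions attributable to the administration of AIT".

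Several design features make time on treatment unequal between patients. Section 2.2.1 admits any product "irrespectively of the selected allergens and the administration route and schedule". Section 2.2.2 records "Adverse events and any reasons for any interruption or switch of AIT", with visits at enrolment and every 12 months for up to 10 years. Section 1 gives the usual course of AIT as three to five years. Section 3.2 cites adherence from 18% to over 90% across studies.

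**The concern.** Whether a patient has had a reaction, and its grade, are qualitative variables, so on a plain reading the rule in section 2.2.5 covers them. The proportion who have ever reacted depends on the reaction rate and on how long patients were exposed. A chi-square or Fisher test on that proportion cannot tell the two apart. If patients leave one product sooner than another, the first has fewer patient-years in which a reaction could occur and can look safer at an identical rate.

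This matters because the registry intends to compare products and phenotypes and, in section 3.2, hopes to give clues about the quality of formulations. It also aims to be large. The bias in the proportions does not shrink as groups grow, so the chance of a spurious significant difference rises with sample size.

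**Working it through.** **What can be checked.** The article states no reaction rate, group size, event count or power, so there is no figure to reproduce. The question is how often the stated test would declare a difference when two groups share the same reaction hazard but differ in time on AIT.

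**Inputs.** From section 2.2.5: the chi-square test at two-sided 0.05. Assumed: a constant hazard h of first reaction of 0.05, 0.10 or 0.20 per year; 200 or 1000 patients per group; a 3-year window; exponential discontinuation with 3-year persistence of 50% in one group and 60% or 70% in the other.

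**Formulas.** Discontinuation rate d = −ln(3-year persistence)/3. Mean time on AIT over 3 years = (1 − persistence)/d. Probability of ever reacting within W years while on AIT = h/(h + d) × (1 − exp(−(h + d)W)).

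**Numbers put in, 50% v 70%, h = 0.10, W = 3.**
- 50% persistence: d = 0.2310; mean time = 0.5/0.2310 = 2.16 years; P = 0.10/0.3310 × (1 − exp(−0.9931)) = 19.0%.
- 70% persistence: d = 0.1189; mean time = 0.3/0.1189 = 2.52 years; P = 0.10/0.2189 × (1 − exp(−0.6567)) = 22.0%.

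The true rates are equal, yet the expected percentages differ by 3 points. The exact binomial probability that the uncorrected chi-square test rejects at 0.05 is then:

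| Scenario | Per group | h = 0.05 | h = 0.10 | h = 0.20 |
|---|---|---|---|---|
| 50% v 60%, 3 years | 200 | 5.7% | 6.8% | 8.5% |
| 50% v 60%, 3 years | 1000 | 9.4% | 13.8% | 22.6% |
| 50% v 70%, 3 years | 200 | 8.0% | 11.5% | 17.9% |
| 50% v 70%, 3 years | 1000 | 21.5% | 37.8% | 63.6% |
| 50% v 70%, first 12 months only | 200 | 5.0% | 5.1% | 5.8% |
| 50% v 70%, first 12 months only | 1000 | 5.8% | 6.5% | 8.2% |

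**Bounds.** If all reactions fall in a first year that every patient completes, exposure is equal where it counts and the test keeps its 5%. At the other extreme, if every patient in one group had 3 years and every patient in the other 5, rejection at 200 per group would be 57.5 / 82.1 / 95.5%. That is an upper bound and not a realistic case.

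**Dependence on when reactions occur.** With 80% of the 5-year cumulative hazard placed in the first 3 months (overall mean rate 0.05 per year) and 1 v 3 years of exposure, the false-positive rate was only about 7% at 200 per group and 11% at 500.

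**Does the remedy work?** Simulation (3000 runs, 50% v 70% persistence, 3 years, no true difference), percentage significant at 1000 per group:

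| Hazard per year | Chi-square | Poisson, offset only | Offset + treatment year | Log-rank | First-year chi-square |
|---|---|---|---|---|---|
| Constant 0.10 | 36.2 | 4.5 | 4.6 | 4.6 | 5.9 |
| 0.20 in year 1, then 0.05 | 19.8 | 9.8 | 5.2 | 5.3 | 8.0 |
| 0.30 in year 1, then 0 | 9.0 | 21.1 | 5.3 | 5.2 | 9.0 |

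Log-rank and the offset with treatment year hold about 5% throughout. An offset alone over-corrects when reactions cluster early. A plain first-year chi-square retains part of the bias, because patients who stop during that year stay in the denominator; in the last row it does no better than the cumulative test.

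**The case against.** The strongest reply is that the article never states the faulted analysis. Section 2.2.5 is a generic list of tests. A frequency in section 2.2.4 could be a count or a rate, and the 12-month visits would allow comparison over equal intervals. A condensed article normally leaves risk windows and censoring rules to the full protocol or analysis plan, which is not shown. Most of the magnitude rests on assumed inputs, and section 3.2 already concedes lower internal validity than a randomised trial.

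Much of this stands. A reader might infer that the registry will test product safety by chi-square on 'ever reacted' data; the article does not say so. A reader might also expect staggered center start to bias the yearly safety comparisons, since "the enrollment in the other centers will start upon approval of each local Ethics Committee" and "The results of the analyses will be published anonymously (as aggregated data) in annual reports". That would require product mix to be linked to center start date and products to be tested against each other at each report. The article supports neither: it gives the periodic analyses a mainly descriptive and quality-control purpose.

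What does not stand is that this is mere missing detail. The article does choose a test for this class of variable, makes no exception for reactions, and names no rate or time-to-event method. The chosen test is a poor default for data with unequal exposure. A general caveat about internal validity does not adjust for time at risk.

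**Conclusion.** The point holds in conditional form. The only comparison stated for qualitative variables takes no account of time on AIT. If it is applied to cumulative yes/no reactions, differences in exposure can appear as differences in safety. This is a risk to guard against and not a demonstrated error.

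The size depends on assumptions that the documents do not supply: the reaction hazard and its timing, the group sizes, and a persistence gap between the groups compared. The design makes time on AIT vary between patients; that it will differ by product or phenotype is plausible but not stated. On the illustrative 50% v 70% persistence with constant hazard, the test's error rises from 5% to 8–18% at 200 per group and 22–64% at 1000 per group. With smaller gaps or early reactions it is much less, and it can be nil. Importance is low to moderate, and confidence in its practical effect is medium.

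**What to change.** Add to section 2.2.5:

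> Between-product and between-phenotype comparisons of adverse reactions use time from AIT start to first reaction (log-rank or Cox), or a Poisson or negative binomial model with log on-treatment time as offset and treatment year as a factor. On-treatment time ends at interruption, switch or last visit. Crude percentages are descriptive only.

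If a first-year comparison is preferred for simplicity, it must also account for on-treatment time within that year, by an offset or by censoring at stopping. It gives up information on later reactions.

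The cost is one paragraph and modest programming, using the product, posology, interruption, switch and visit records already planned. Precision is limited by how exactly stop and reaction dates are recorded; if only the 12-month visits are available, the model by treatment year is the feasible version.

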Continuing in the footsteps of the general review of updated evidence on the efficacy of AIT, especially in asthma [22,45], questions on the sustainability and general cost-effectiveness of this therapy have recently arisen, despite the fact that past pharmacoeconomic studies and cost-utility analyses have generally reported that AIT is economically advantageous [20]. The already mentioned review of Dhami S. et al. [45] took into consideration three studies as the best conducted on this topic and all three demonstrated an economic advantage in treating allergic asthmatic patients with AIT [83,84,85]; nevertheless, even these three studies were not without flaws and yet again there is a lack of robust long-term information in different social-economic settings. The discussion on the economic sustainability of AIT and its cost-effectiveness ratio is still open [86].

Finally, there is a problem with standardizing allergen extracts and formulations. For the common allergens, many companies provide characterized, standardized, and stable preparation for AIT. However, there is also an urgent need for a thorough harmonization of international standards in AIT [82] due to the highly heterogeneous regulation across different countries [87]. Indeed, in non-standardized preparations, the exact amount of the allergen extract might vary between batches [88,89]. In fact, some products might benefit from appropriate studies [90]. RIAIT, confronting different available products and registering their outcomes on heterogeneous patients, might provide clues on the quality of some of these formulations and help measure their impact on the patient’s disease.

Certain limitations of RIAIT should be acknowledged. Firstly, as already summarized, the quality of a registry depends on the quality of the data it contains (e.g., what is measured, in whom, how, and the extent of missing data). Secondly, due to their design, registry data might possess intrinsic lower internal validity than data collected in RCTs, limiting the extent to which they can support causal relationships.

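### The statistics section names only unadjusted tests that assume independent patients for group differences, and ties no adjusted or centre-aware model to the product-effectiveness objective

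*Protocol article*

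**What the plan says.** Section 2.2.5 of the protocol article gives the methods for group differences. For quantitative variables: "Differences between groups among quantitative variables are analyzed via Student’s t-test or Mann–Whitney, on the basis of their distribution". For categorical variables: "Differences between groups among qualitative variables will be analyzed with the chi-square test or Fisher’s exact test depending on their distribution". The threshold is also fixed: "A two-tailed *p*-value with values inferior to 0.05 will be considered significant".

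Two further sentences in the same section list models. One reads: "Multivariate or univariate linear regression analyses will be performed among the variables based on a 95% confidence interval". The other names GEE and GLM, with the stated purpose that they "will be used to identify responders and non-responders". Neither names an exposure, a covariate or a centre term. In the statistics, centre appears only as a unit for reporting recruitment, completeness and patient characteristics.

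The comparative aim is stated in two places. The first objective in section 2.2.3 is: "Evaluate the short- and long-term real-life effectiveness and safety of AIT overall, in specific patient groups’ phenotypes and with specific AIT products". Section 3.2 adds: "RIAIT, confronting different available products and registering their outcomes on heterogeneous patients, might provide clues on the quality of some of these formulations". Treatment comes by prescription. The inclusion criterion in section 2.2.1 reads: "Having received the prescription of any of the available AIT products in Italy, irrespectively of the selected allergens and the administration route and schedule".

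**The concern.** A t-test, Mann–Whitney, chi-square or Fisher test answers a product question only if the product groups are comparable and the patients independent. Neither can be taken for granted in this registry. A physician chooses the product, and section 2.2.3 makes the factors behind treatment choice a subject of study, so the authors expect choice to depend on patient and setting. Patients are recruited through a network of centres. Outcomes are recorded at enrolment and every 12 months, yet a two-sample test uses neither the baseline value nor the repeated measures. Student's t and Mann–Whitney also compare only two groups at a time, while many products are eligible.

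Two distinct errors can follow. If a product is preferred for sicker patients, or in centres with generally better or worse outcomes, the contrast is biased. If product choice also differs between centres and outcomes correlate within them, the standard error is too small. The bias does not shrink as the registry grows; a larger registry only makes it more likely to reach p<0.05. This matters because section 3 relies on the volume of data for statistical power.

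**Working it through.** **Inputs from the article.** Two-sided alpha 0.05; the tests named in section 2.2.5; assignment by prescription; a multicentre network. The article states no sample size, number of centres, ICC, SD or effect size, so it has no figure of its own to reproduce. Everything below except alpha is an assumption.

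**1. Clustering, no true product difference.** Take *m* = 50 patients per centre, ICC = 0.05 and two equally used products. Let *s* be the share of the variance in product choice that lies between centres.

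- Design effect: DE = 1 + (*m* − 1) × ICC × *s*
- Real type I error: 2 × [1 − Φ(1.96/√DE)]
- If each centre uses its preferred product in 80% of patients, *s* = (0.8 − 0.5)²/(0.5 × 0.5) = 0.36. DE = 1 + 49 × 0.05 × 0.36 = 1.88, and the real error is about 15%.
- If each centre uses one product only, *s* = 1. DE = 1 + 49 × 0.05 = 3.45, and the real error is 29.1%.

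| Product choice (ICC 0.05, *m* = 50) | Formula | Simulated t-test |
|---|---|---|
| Equal mix in every centre | – | 4.5% (30 centres) |
| 80% centre preference | about 15% | 15.6% (20 centres) |
| One product per centre | 29.1% | 27.8% (20 centres), 28.7% (30 centres) |

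The simulations used 3,000 runs (20 centres) or 4,000 runs (30 centres).

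Range over ICC:
- 80% preference, 20 centres of 50: 8.8%, 15.6% and 24.6% for ICC 0.02, 0.05 and 0.10.
- One product per centre, by formula with *m* = 50: 10.8%, 29.1% and 42.0% for ICC 0.01, 0.05 and 0.10.
- Equal mix, 30 centres of 50: 5.1%, 4.5% and 3.3% for ICC 0.01, 0.05 and 0.10. There is no inflation, and the test becomes slightly conservative.

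With a centre-adjusted analysis, rejection returns to 5.5% (ICC 0.05) and 5.0% (ICC 0.10) under 80% preference. It stays between 4.6% and 5.7% in all the 30-centre scenarios. Where each centre used one product only, the adjusted analysis compared centre means.

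**2. Confounding by severity, no true product difference, no clustering.** Let *d* be the baseline imbalance in SD and *r* the correlation between baseline and follow-up.

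- Bias of the unadjusted follow-up contrast: *r* × *d* = 0.6 × 0.3 = 0.18 SD.
- With 250 per product, SE = √(2/250) = 0.089 and 0.18/0.089 = 2.01, so p<0.05 occurs about 52% of the time. With 500 per product it occurs about 81% of the time.
- An unadjusted change score errs the other way: (*r* − 1) × *d* = −0.4 × 0.3 = −0.12 SD.

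Milder alternatives, using a binary severity marker:
- A 20-point prevalence difference with a 0.5 SD effect gives a bias of 0.2 × 0.5 = 0.10 SD, significant in 10.9%, 20.1% and 49.1% of cases at 100, 250 and 750 per product.
- A 10-point difference with a 0.3 SD effect gives 0.1 × 0.3 = 0.03 SD, significant in 5.5%, 6.3% and 8.9%.

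**The case against.** The strongest reply is that section 2.2.5 never says which groups the two-sample tests compare. It opens with enrolment, completeness and descriptive tables by centre, and such tests suit that use. Multivariable regression and GEE/GLM follow soon after. A covariate list or cluster unit may properly sit in the full protocol or SAP, which are not shown. The article concedes in section 3.1 that registries lack randomisation, and in section 3.2 that they give limited support for causal claims. The product statement in section 3.2 is itself hedged.

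Much of this stands. A reader might infer that product, route and phenotype comparisons are expressly planned as unadjusted two-sample tests. The text does not say so: the groups are unnamed, and route does not appear in the effectiveness objective. Phenotypes are patient characteristics, not something a physician selects, so the argument about treatment choice does not apply to them. A missing covariate list is not a fault in an article.

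The point survives for three reasons. The only methods given for group differences are unadjusted. In the regression sentence, univariate models stand as an equal alternative to multivariate ones. GEE/GLM carries a different stated purpose. Responder status could turn out to be the effectiveness outcome, but the article does not link it to product comparisons. The acknowledged limitations change no analysis.

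**Conclusion.** The point holds in a limited form. Section 2.2.5 fixes unadjusted tests that assume independence for group differences. It also lists models that could adjust, but ties none of them to the product objective or to centre. Product contrasts made with the named tests can be confounded by severity and centre, in either direction.

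A reader might also infer that product differences will be declared significant too often. The documents do not support that as a certainty. Inflation from clustering needs product choice that varies by centre and correlation of outcomes within centre. Both are plausible, and neither is stated. On the assumptions above (ICC 0.05, 50 patients per centre), the real type I error runs from about 5% or slightly below with equal mix, through about 15% with 80% preference, to about 28–29% with one product per centre. The 0.18 SD spurious difference likewise depends on the assumed 0.3 SD imbalance and 0.6 correlation; milder assumptions give 0.03 to 0.10 SD. These figures show what the named tests allow; they do not predict this registry's error rate.

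**What to change.** In section 2.2.5:

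- Limit Student's t, Mann–Whitney, chi-square and Fisher tests to description.
- State that outcome comparisons between products (and between routes, if these are compared) use a multivariable model with all products entered together. Adjust for the baseline value of the same outcome and for confounders already collected under section 2.2.2: age, disease (rhinitis, conjunctivitis, asthma), sensitisation profile and baseline drug therapy.
- Account for centre by a random or fixed effect or by cluster-robust errors, and allow for the repeated yearly measures. Where centres use a single product, a fixed centre effect cannot be separated from the product, so a random effect or an analysis at centre level is needed there. Cluster-robust errors correct the standard error but do not remove confounding by centre.
- For phenotype comparisons, account for centre and adjust only for variables that do not define the phenotype. Otherwise the contrast of interest may be adjusted away.

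Propensity weights, partial pooling of products and false-discovery control are optional.

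The cost is a change of wording and no new data. Intervals will be somewhat wider for products concentrated in few centres. The change should be made before any product comparison enters an annual report or publication.
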